# Early intervention, treatment and rehabilitation of employees with common mental disorders by using psychotherapeutic consultation at work: study protocol of a randomised controlled multicentre trial (friaa project)

**DOI:** 10.1186/s12889-021-11195-9

**Published:** 2021-06-22

**Keywords:** Mental health, Workplace, Return to work, Psychotherapy, Depression, Self-efficacy, Sickness absence

## Abstract

**Background:**

Common mental disorders are one of the leading causes for sickness absence and early retirement due to reduced health. Furthermore, a treatment gap for common mental disorders has been described worldwide. Within this study, psychotherapeutic consultation at work defined as a tailored, module-based and work-related psychotherapeutic intervention will be applied to improve mental health care.

**Methods:**

This study comprises a randomised controlled multicentre trial with 1:1 allocation to an intervention and control group. In total, 520 employees with common mental disorders shall be recruited from companies being located around five study centres in Germany. Besides care as usual, the intervention group will receive up to 17 sessions of psychotherapy. The first session will include basics diagnostics and medical indication of treatment and the second session will include work-related diagnostics. Then, participants of the intervention group may receive work-related psychotherapeutic consultation for up to ten sessions. Further psychotherapeutic consultation during return to work for up to five sessions will be offered where appropriate. The control group will receive care as usual and the first intervention session of basic diagnostics and medical indication of treatment. After enrolment to the study, participants will be followed up after nine (first follow-up) and fifteen (second follow-up) months. Self-reported days of sickness absence within the last 6 months at the second follow-up will be used as the primary outcome and self-efficacy at the second follow-up as the secondary outcome. Furthermore, a cost-benefit assessment related to costs of common mental disorders for social insurances and companies will be performed.

**Discussion:**

Psychotherapeutic consultation at work represents a low threshold care model aiming to overcome treatment gaps for employees with common mental disorders. If successfully implemented and evaluated, it might serve as a role model to the care of employees with common mental disorders and might be adopted in standard care in cooperation with sickness and pension insurances in Germany.

**Trial registration:**

The friaa project was registered at the German Clinical Trial Register (DRKS) at 01.03.2021 (DRKS00023049): https://www.drks.de/drks_web/navigate.do?navigationId=trial.HTML&TRIAL_ID=DRKS00023049.

**Supplementary Information:**

The online version contains supplementary material available at 10.1186/s12889-021-11195-9.

## Background

Common mental disorders (CMDs) are one of the major public health problems worldwide with an estimated twelve-month global prevalence rate of 17.6% [1]. According to their high burden of disease [2], CMDs are one of the leading causes for sickness absence [3] and go along with high risks of early retirement [4]. Prevention, early treatment and well-concerted reintegration after sickness absence might act as key factors to reduce the risk of chronicity of CMDs, long and recurrent sickness absence and early retirement due to CMDs. However, even in high-income countries, large treatment gaps were reported. For example, only 5 % of individuals with anxiety disorders and 22% of individuals with major depressive disorders are estimated to receive adequate treatment [5, 6]. On the one hand, reasons for this treatment gap are supposed to be person-related including lack of perceived need for treatment [5] and fear of stigmatisation [7, 8]. On the other hand, reasons are related to the health-care system itself including long waiting times on therapy [9–11].

Psychotherapeutic consultation at work is a new and low threshold concept for early prevention and treatment of employees with symptoms of CMDs [12, 13]. It might offer first consultation, diagnostic identification, referral to care as usual (CAU), proceeding psychotherapy, and therefore possibilities to tackle treatment gaps regarding mental health [14]. First evidence suggests that psychotherapeutic consultation at work significantly reduces depressive symptoms and anxiety and improves work ability [15]. In addition, extrapolation suggests that screening of CMDs and subsequent psychotherapeutic treatment at work is cost effective [16]. Furthermore, psychotherapeutic consultation at work can serve as a model for close collaboration between occupational health physicians, psychotherapists and other mental health care providers [17]. Such collaboration has been regarded as an additional key factor to improve treatment and return to work (RTW) of employees with CMDs [18]. For example, within a previous randomised controlled trial (RCT), referral of employees with depression to psychiatric care by occupational health physicians was combined with collaboration between those health care providers during vocational reintegration. This intervention was found to be associated with faster RTW compared to CAU [19]. More successful and sustainable RTW might further be achieved by combining CAU and work-related psychotherapy as evidenced by previous research [20–26]. Concepts of work-related psychotherapy were most often developed to support vocational reintegration of employees being sick-listed due to CMDs, including - inter alia - work-related assessments, assistance in drawing RTW plans and contacting employers and occupational physicians as well as evaluation of RTW steps [19–24]. However, work-related psychotherapy could also contribute to reduction of depressive symptoms and improvement of work ability at earlier stages [27, 28].

Particularly a combination of a) prevention, b) early treatment, c) work-related psychotherapy and d) collaboration between key (mental) health care professionals might help to tackle the reported treatment gap and therefore chronicity, long and recurrent sickness absence and early retirement due to CMDs. However, within occupational settings, previous studies have mainly investigated the effectiveness of interventions addressing either one or two of those aspects (e.g. [15, 21, 22, 24, 27, 28]). Furthermore, study samples were often small including only one or two companies and cost-benefit assessments are seldom performed (e.g. [15, 19, 25, 27, 28]). RCTs testing the effectiveness of more comprehensive care models in small, middle as well as large-sized companies are scarce.

This two-arm randomised controlled multicentre trial - called early intervention in the workplace (German: Frühe Intervention am Arbeitsplatz, friaa) - therefore aims to evaluate psychotherapeutic consultation at work, which in this study consists of a tailored, module-based and work-related psychotherapeutic intervention. The intervention will thereby combine the four aspects of prevention, early treatment, work-related psychotherapy and collaboration between key (mental) health care professionals. Employees with symptoms of CMDs will be randomised with 1:1 allocation to an intervention group receiving psychotherapeutic consultation at work or to a control group receiving CAU. Participants’ outcome data of both groups will be collected nine (first follow-up) and fifteen (second follow-up) months after enrolment.

The primary aim is to investigate whether the intervention is superior to CAU regarding reduction of sickness absence within the last 6 months at the second follow-up among employees with symptoms of CMDs.

The secondary aims are to investigate whether the intervention is superior to CAU regarding
levels of occupational self-efficacy at the second follow-up among employees with symptoms of CMDsa health economic evaluation related to costs of CMDs for social insurances and companies at second follow-up

## Methods/design

### Participants, interventions, and study variables

#### Study setting and recruitment

Participants will be recruited from small, middle and large-sized companies being located around five study centres in Germany (in and around Ulm, Düsseldorf, Teltow, Hildesheim and Erlangen) over a period of twelve months, starting in September 2021. Psychotherapeutic consultation at work will be established in close collaboration with occupational health services in or outside of business premises based on preferences of participating companies. Employees with psychological complaints will then be transferred to psychotherapeutic consultation at work by occupational health physicians, supervisors or by self-assignment. Each employee who is transferred to psychotherapeutic consultation at work will receive diagnostic assessment regarding mental health and recommendations for further procedures in CAU (Module 1-A). They will be screened for eligibility criteria and if eligible, will be asked to participate by written informed consent. Participants will then be randomised to the intervention group or control group with 1:1 allocation. Participants not meeting the eligibility criteria will get the according recommendation to CAU. The intervention modules will be accompanied by setting up a network of occupational health services, psychotherapists conducting the psychotherapeutic consultation, clinics for psychosomatic medicine and rehabilitation centres depending on local conditions. Communication between those (mental) health care providers will be established in the form of standardised handovers. Furthermore, educational programs will be offered to all occupational physicians and psychotherapists taking part in the intervention.

#### Eligibility criteria

Inclusion criteria:
written informed consent to participate in the studyaged 18 years or abovesufficient knowledge of the German language to participate in the studyemployment for at least 15 h per week in participating companiesdiagnosis of a CMD according to the International Statistical Classification of Diseases and Related Health Problems (ICD-10 [29]) including unipolar depressive disorders (F32-F34), anxiety disorders (F40, F41), stress-related and somatoform disorders (F42, F43, F45, F48.0) and non-organic sleep disorders (F51) or subclinical symptoms of psychosomatic disorders without ICD-10 diagnosissymptoms of psychosomatic disorders without ICD-10 diagnosis measured by the Global Assessment of Functioning Scale (GAF Scale < 81, [30, 31]).

Exclusion criteria:
unique or main diagnosis of substance abuse (F10–19), schizophrenia, psychosis (F20-F29) or organic psychiatric disorders (F00-F09)severe and unstable somatic health condition (e.g. cancer)current psychotherapeutic treatmentapplication for retirement pension

#### Intervention

All sessions of psychotherapeutic consultation at work will be conducted by licenced psychological or medical psychotherapists or by psychological or medical psychotherapists being in an advanced state of postgraduate training for psychotherapy. The intervention consists of three modules. The first module includes one session of basic diagnostic assessment on mental health (Module 1-A) and one session of work-related diagnostic assessment (Module 1-B). Whereas Module 1-A will be offered to the intervention and control group, Module 1-B and all other modules will exclusively be offered to the intervention group. Based on mental health assessment, participants of the control group will receive recommendations for treatment in CAU (e.g. in- or outpatient acute care, inpatient vocational rehabilitation). Participants of the intervention group will be transferred to CAU if outpatient work-related treatment would not sufficiently cover the individual need for treatment or will receive Module 2. In case participants of the intervention group are transferred to CAU, potential waiting times for treatment will be bridged by Module 2. Module 2 will include up to ten sessions of work-related psychotherapeutic consultation or treatment. Participants of the intervention group with an inability to work will receive further psychotherapeutic consultation during their RTW process in up to five sessions during Module 3. Participants of the intervention group may thus receive up to 17 sessions of psychotherapeutic consultation (Module 1-A: one session; Module 1-B: one session; Module 2: ten sessions; Module 3: five sessions). For both, the control and intervention group, a medical report will be prepared. Participants of the intervention group who received up to four sessions of psychotherapeutic consultation and participants of the control group will receive a follow-up call by study therapists twelve weeks after their last visit. In this call, participants will be asked on how they have coped so far and whether further help regarding treatment in CAU is needed. For all other participants, an equal follow-up will be performed during their last session of psychotherapeutic consultation.

A schematic overview of the intervention is given in Fig. 1 and all its components are further described below.

**Fig. 1 Fig1:**
[figure not shown]
Overview on study intervention

##### Module 1-a. basic clinical assessment

Medical and psychosomatic historyInternational Neuropsychiatric Interviews (MINI [32])Screening of eligibility and inclusion in the studyRandomisation of participants into intervention or control groupRecommendations for further procedures in CAU (e.g. in- or outpatient acute care, inpatient vocational rehabilitation)Participants of the intervention group may further be referred to the second module of the intervention.

##### Module 1-B. work-related assessment

Work-related assessment including work history, job description, work tasks, work relationships and person-job fit as described elsewhere [25, 33]. If possible, information on those aspects being provided by occupational physicians will also be taken into accountAnalysis of working conditions, social conflicts and social-therapeutic aspects including general social problems or concealed resources as described by Köllner [34]

##### Module 2. Work-related psychotherapeutic intervention

During module 2, an adaption of the manual from Bode et al. [33] will be used to conduct work-related psychotherapeutic consultation. This will include
Psychoeducation providing information on the relations between work and mental healthFormation of an individual exploratory model of current psychosomatic symptoms. In this model, stressors and resources at work will be includedUsing communication techniques to increase, maintain or restore motivation to workDefining achievable tasks as well as focusing on achievements and resources at work to promote self-efficacyDiscussing problems at work, elaboration of solution approaches and searching for contact persons at work to implement those solution approachesEvaluation and treatment of work-related symptoms (e.g. anxiety or overload) by using cognitive restructuring methodsImplementation of work-related cognitive-behavioural therapeutic treatment measures: resource activating measures, relaxation techniques that can be used at the workplace, coaching of social competences, communication exercises, acceptance of unchangeable situations, clarification of intrapersonal conflicts, promotion of acceptance and emotional competenceDetection of work-related risk factors for development and deterioration of CMDs (e.g. shift work) and giving recommendations of setting-based prevention measures to minimise them

Depending on severity of symptoms, psychotherapeutic consultation during module 2 may either include more curative or preventive aspects. Therefore, module 2 is subdivided into module 2-A comprising work-related short-term psychotherapy and module 2-B comprising work-related prevention. Module 2-A contains both disorder specific psychotherapeutic interventions and the above mentioned work-related interventions. Participants with an ICD-10 diagnosis will thus receive module 2-A and participants with subclinical psychosomatic symptoms without an ICD-10 diagnosis will receive module 2-B.

##### Module 3. Psychotherapeutic consultation during RTW

RTW should be prepared and implemented in consideration of the four phase model of vocational reintegration [35]. Therapeutic sessions of module 3 will be offered to participants with prior sickness absence to support RTW. This will include the implementation of therapeutic issues and strategies from module 1-B and 2. Furthermore, module 3 will comprise
Psychotherapeutic support and evaluation of each reintegration step (e.g. discussion of successful and unsuccessful aspects or needs for adjustments of the reintegration plan) as described by Bode et al. [33]If the patient provides informed consent, study psychotherapists will be involved within the occupational process of reintegration and will collaborate with responsible RTW actors (e.g. occupational physician)

Weekly sessions will be intended.

##### Handovers

Accompanying all modules of the interventionStandardised forms for communication between occupational physicians, psychotherapists and other care providersHandovers will only be performed with patient’s permission under consideration of medical confidentiality and data protection legislation

##### Contents of educational programs for psychotherapists and occupational physicians

Applications for rehabilitation measures in the German health care systemDraft of medical reports to increase efficient communication between health care providersInformation on aims, processes and regulations of prevention and rehabilitation offers of sickness and pension insurances in GermanyCulture-specific approaches during treatment according to Erim et al. [36]Additional contents within the educational program for psychotherapists: training in the intervention modules and basic knowledge about occupational health careAdditional contents within the educational program for occupational health physicians: Psychotherapeutic primary care

#### Discontinuation and modifications of the intervention protocol

The intervention might be discontinued if symptoms decrease and there is no indication for further treatment. If an appointment has been missed, efforts will be made to contact the participant to schedule a new appointment. However, in case that a participant refuses further treatment, the intervention will be discontinued and participants will be asked for their reasons for refusal. If symptoms increase, the psychotherapist and possibly supervisor (i.e. a versed psychotherapist) will weight up further treatment needs. They might schedule a higher frequency of therapy sessions - but no more than 10 sessions of module 2 and 5 sessions of module 3 - or might refer participants to inpatient care. In each case, participants will remain in the study and will be reminded of the follow-up measurements in their last therapy session.

If participants withdraw their informed consent to participate in the study, further therapy sessions will be cancelled. In this case, follow-up measurements will not be performed. If participants also withdraw their informed consent of data storage, collected data of those participants will be deleted and not be included within data analysis.

In general, concomitant care and interventions (e.g. outpatient psychiatric or neurological treatment, somatic treatment, non-medical practitioner treatment, psychological coaching, use of helplines and helpdesks at work) are not prohibited during the trial. Moreover, module 2 aims to bridge waiting times on CAU and therefore also outpatient psychotherapeutic and inpatient psychotherapeutic, psychiatric or rehabilitation treatment are not prohibited during the trial. However, the intervention will be terminated or paused during CAU. Employees receiving psychotherapeutic treatment before starting the intervention are excluded from the study.

In general, discontinuation and all deviations of the intervention protocol will be documented.

#### Adherence to the study protocol

Several strategies will be implemented to ensure adherence to the intervention protocol. First, psychotherapists will be trained in the intervention modules during the two-day educational program. Second, psychotherapists will be constantly supervised by a versed therapist and a scientific assistant from the study. Third, therapists will be instructed to record defined treatment sessions on video. The manual from Bode et al. (2017) served as a basis for selecting important interventions [33]. For the evaluation of treatment integrity only those treatment sessions that contain the interventions will be recorded and analysed. Assignment to intervention modules, number of sessions in each module and session dates will be documented and completeness of data will be constantly monitored during the intervention by the psychotherapists and scientific assistants. Furthermore, participants will be regularly reminded of follow-up measurements.

#### Outcomes

##### Primary outcome

Days of sickness absence within the last 6 months at second follow-up will serve as the primary outcome. As in comparable previous studies [25, 37], days of sickness absence is chosen as the primary outcome due to its economic value and because it is a relevant parameter of psychotherapeutic and psychiatric rehabilitation measures. Days of sickness absence within the last 6 months will be collected as a self-reported item by standardised paper-and-pencil or online questionnaires during baseline and during follow-ups. This item was self-developed for this study. Participants will be asked whether they were absent from work for health reasons within the last 6 weeks with response options “yes” and “no”. If participants ticked “yes”, they will be asked about the number of days of sickness absence within the last 6 months excluding regular non-working days.

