### Assignment of interventions

#### Allocation

Eligible participants will be allocated concealed by randomisation using a centralized web based tool (www.randomizer.at) after Module 1-A. Stratification by centre, days of sickness absence within the last 6 months (< 21 days vs. ≥ 21 days) and level of depression measured by the Patient Health Questionnaire-9 (PHQ-9 [54, 55]; ≤ 10 vs. > 10) using block randomisation of variable sizes will be performed.

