#### Statistical methods

The treatment effect on the primary outcome (days of sickness absence within the last 6 months at the second follow-up) will be analysed using a mixed negative binomial regression model. Treatment group, days of sickness absence within the last 6 months before baseline, gender, age, subjective work ability at baseline as well as the centre will be included as covariates and the respective company as random effect. The primary analysis will be conducted based on the full analysis set according to the intention-to-treat (ITT) principle (i.e. all patients will be analysed in the group they were randomised to).

Missing data for the primary and secondary outcome analysis is assumed to be “missing at random” and replaced using multiple imputation based on predictive mean matching using the covariates of the primary and secondary outcome analysis as potential predictors [75].

As a sensitivity analysis, an evaluation based on the per-protocol (PP) population will be performed. The PP set consists of all participants without major protocol violations. For this analysis, no imputation of missing data will be performed.

In case of significance of the ITT analysis of the primary outcome (two-sided confidence level of 5%), a hierarchical linear mixed model will be used to analyse treatment effects on self-efficacy. This model will include treatment group, self-efficacy at baseline, gender, age, subjective work ability at baseline as well as the centre as covariates and company as random effect. Applying this hierarchical testing strategy, the overall type I error rate will still be controlled.

If no significance of the ITT analysis is achieved, the results of this analysis will be interpreted only in a descriptive sense.

Furthermore, subgroup analyses will be performed to evaluate the role of additional variables (e.g. indication of treatment, type of treatment, symptom severity) on treatment effects on the primary and secondary outcome.

Further collected data (see Table 1) will be analysed using appropriate descriptive methods.

Details of the statistical analysis will be further determined in a statistical analysis plan which will be written before database closure.

All those analyses will be conducted using SAS 9.4 or higher.

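### The primary-outcome item filters on absence in the last 6 weeks but counts days over 6 months, so as printed, absence that ended earlier is never counted

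*Protocol article*

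**What the plan says.** The Primary outcome section sets the endpoint: "Days of sickness absence within the last 6 months at second follow-up will serve as the primary outcome". It then describes a two-step item. Step one: participants are "asked whether they were absent from work for health reasons within the last 6 weeks", to be answered yes or no. Step two, reached only after a yes: "they will be asked about the number of days of sickness absence within the last 6 months excluding regular non-working days". The section adds "This item was self-developed for this study" and says the item is given at baseline and at the follow-ups.

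The same quantity appears in two other places, each time with a six-month window. Under Allocation: "Stratification by centre, days of sickness absence within the last 6 months", cut at 21 days. Under Statistical methods, the covariates of the primary model are listed as "Treatment group, days of sickness absence within the last 6 months before baseline, gender, age, subjective work ability at baseline", together with centre.

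The Abstract, the stated aims in the Background and the Sample size calculations also use six months. The 6-week window occurs only in the filter question. The Additional data section says the wording of this item is in the supplementary material, which is not shown here.

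**The concern.** A filter question should let through everyone who could have a non-zero answer to the question behind it. This one does not. A participant whose absence ended seven or more weeks before the questionnaire truthfully ticks no and is never asked how many days were missed. Nothing in the article describes another route by which those days would be recovered.

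The recorded value would then depend on when absence fell as well as on how much there was. This is the primary endpoint, and a count that was never asked for cannot be restored at the analysis stage. Because the item is repeated at baseline, the fault would carry into the baseline covariate and, if the stratification value comes from the same item, into the stratum.

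**Working it through.** **Windows.** Filter: 6 weeks. Endpoint and count: 6 months, about 26 weeks. Share screened: 6/26 = 23%. Unscreened: 26 − 6 = 20 weeks, or 20 × 5 = 100 working days in a five-day week. Planned difference at follow-up (Sample size calculations): 42 − 26 = 16 days.

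**If no is coded 0.** Someone absent at any time in the unscreened 20 weeks, but not in the last 6, is entered as 0. The error for one person can reach about 100 days.

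**If no is coded missing.** Statistical methods would then fill the value by predictive mean matching, assuming missing at random. Every observed donor has been absent in the last 6 weeks, so every donor value is positive. True zeros would be replaced by positive counts. Under the planned negative binomial model with dispersion k = 2.12, the share of true zeros is (1 + k·mean)^(−1/k): 15% at mean 26 and 12% at mean 42. The per-protocol analysis, which imputes nothing, would keep only recently absent people.

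**Illustrative size, with no coded 0.** Assumptions, none of them from the document except the means, k = 2.12 and the SD: negative binomial days with means 26 and 42, capped at 130 working days; absence placed at random as one block or in spells of about 10 or 5 days; the same placement rule in both arms; filter on the last 30 working days. The second dispersion comes from the stated SD: (35² − 36)/36² = 0.92.

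| k | Spells | Absentees ticking no, mean 26 / mean 42 | Ratio, full count | Ratio, recorded |
|---|---|---|---|---|
| 2.12 | one block | 65.2% / 58.3% | 0.690 | 0.580 |
| 2.12 | about 10 days | 46.5% / 38.1% | 0.688 | 0.642 |
| 2.12 | about 5 days | 36.1% / 30.0% | 0.689 | 0.665 |
| 0.92 | one block | 68.3% / 60.0% | 0.645 | 0.482 |
| 0.92 | about 10 days | 44.5% / 32.8% | 0.639 | 0.566 |
| 0.92 | about 5 days | 31.9% / 22.3% | 0.644 | 0.604 |

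The full-count ratio differs from 26/42 = 0.619 because of the cap. With k = 2.12, recorded zeros rise from 12–15% to 38–71%.

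**Direction.** It depends on which arm loses more days. If the filter removes 20% of control days and 40% of intervention days, the ratio is (26 × 0.6)/(42 × 0.8) = 15.6/33.6 = 0.464. With the losses reversed it is (26 × 0.8)/(42 × 0.6) = 20.8/25.2 = 0.825. Equal losses leave 0.619.

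**Sample size.** The plan gives no figure for the filter; its sample size rests on full six-month means. With V = 1/42 + 1/26 + 2 × 2.12 = 4.302, n per arm = (1.960 + 0.842)² × 4.302 / ln(26/42)² = 147. Entering the means as monthly rates (7.00 and 4.33) gives 155 to 157 under common variance choices, in line with the stated 155. For dropout, 310/0.60 = 517, against 520 planned. No input changes when the filter is corrected.

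**The case against.** The strongest reply is that 6 weeks is a slip in the article. Every other mention says six months, no reason is given for a 6-week screen, and the real item sits in a supplement not seen here. This stands as a limit on the claim. A reader might infer that the trial will in fact field a 6-week filter; the document shows only that its own description of the item is inconsistent. It does not remove the point, because the published outcome definition is then wrong and still needs correcting.

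Other stronger readings also go beyond the document:

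- **That a no is scored as zero days.** This is the natural result of a skip, but the coding is not stated.
- **That the stratum is certainly misclassified.** Allocation does not name the source of the 21-day value. The item is the only source described, and Blinding has baseline variables collected before allocation, so the link is probable. Misclassifying a stratum or covariate would cost precision; it would not by itself bias a randomised comparison.
- **That extra zeros inflate the variance.** Relative dispersion rises, but the mean falls too. In one set of simulated spell patterns the squared coefficient of variation rose 1.5- to 1.8-fold while 17% to 28% of days were lost. That implies variance ratios of about 1.5 × 0.83² = 1.03 and 1.8 × 0.72² = 0.93.
- **That the filter favours the intervention by rewarding earlier return to work.** Timing could differ by arm, since Module 3 supports return to work and the Discussion expects later treatment in controls. But the outcome window is months 9 to 15, and no arm-specific timing is given or was modelled.

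**Conclusion.** The point holds as an internal contradiction in the definition of the primary outcome. Followed as printed, the item does not measure six-month absence, whether a no is coded 0 or missing. This conclusion needs only the two windows and the skip, and no simulation.

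The size is uncertain. What is firm is that 23% of the window is screened and that up to about 100 working days per person could be lost, against a planned difference of 16. The shares of 22% to 68% ticking no, and shifts such as 0.69 to between 0.58 and 0.67, rest on assumed spell patterns, a common timing rule in both arms and coding as 0. They show that the effect could matter; they do not estimate it. The direction of any bias between arms is not established.

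**What to change.** Before the first participant is enrolled (recruitment is planned from September 2021), compare the supplementary questionnaire and the eCRF skip rule with the endpoint definition.

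- If the 6-week filter is there, change it to the last 6 months at baseline and at both follow-ups, or drop it and ask everyone for the number of days with 0 allowed. The second option also settles how a no is coded.
- If the fielded item already says six months, correct the outcome description in the published protocol.
- State in the protocol that the stratification value comes from this item, if it does.

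The cost is a change of wording and one skip rule. The sample size is unaffected. After data collection, the missing counts could not be recovered from anything the article describes.
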